#### **Routine Record keeping:**

The first-level health workers LHWs/CMWs will maintain their own records of visits and maternal and birth outcomes as per standard existing HMIS data collection formats. The health facility staff will keep their record of in and out patient admission with causes and outcome on standardized data collection forms. This exercise will be coupled with the collection of HMIS and MIS data from first level health workers and health facilities by the project staff on monthly basis. The information on referral pattern and tracking of cases will also be documented.

We plan to have a dedicated senior data collection supervisor tasked with collecting and collating data on referrals and allocating household numbers. The main data for analysis will come from the ongoing surveillance for pregnancies, birth outcomes and the household level pregnancy tracking system. As indicated earlier, the two routine systems for data collection from LHW registers and the MIS system from health facilities will be used to complement existing program implementation and feedback by LHW supervisors. We aim to specifically introduce two indicators (LHW attendance at birth and an additional post natal visit within 48 hours) for program monitoring purposes and to provide LHW supervisors with the information for regular follow up with concerned LHWs in the intervention clusters.

This information will also be cross-checked against the data collected independently by the surveillance teams, but will not be the basis for analysis of primary outcomes.

### **Active Surveillance**

We will also conduct active surveillance in the community to obtain vital statistics in the communities of all arms of the study and to evaluate the trends between intervention and control clusters over time. Special data collection teams will be constituted and will work independent of LHWs and other health staff. These data collection teams will collect information from each village on;

- movement of households members and additional population influx
- pregnancies
- live births, stillbirths, neonatal & maternal deaths
- cases of birth asphyxia, sepsis and low birth weight infants,
- Maternal and neonatal referrals etc.

The data will be collected and recorded on standardized forms by a regular system of community visits and also cross-checked by reviewing local hospital records.

At the end we will evaluate the impact of the interventions on the target population. The evaluation will concentrate on impacts of development and implement intervention package for community-level care workers in representative study areas aimed at reducing postpartum maternal and neonatal mortality and morbidity. The results of last surveillance round will be compared with baseline findings, and impact assessment of the interventions will be made on the major domains of evaluation including:

- Design.
- Impact on the primary and secondary outcomes.
- Program efficiency.

### **Study Outcome & Process Indicators (at the end of each yr (total 3)**

The primary outcome variables will be:

- All cause neonatal mortality rate
- Perinatal mortality rate

Secondary outcomes

- All cause maternal mortality
- Cause specific maternal mortality such as deaths related to postpartum hemorrhage, puerperal sepsis, eclampsia, obstructed labor, unsafe abortion and indirect causes
- Maternal morbidity such as (including obstetric fistula, eclampsia and obstetrical sepsis
- Cause specific neonatal mortality such as deaths related to birth asphyxia, prematurity, and sepsis.

The key process indicators include:

1. Proportion of women attended by CMWs/LHWs for ANC

2. Proportion of women supplemented with iron/folate
3. Proportion of women received TT immunization
4. Proportion of births attended by CMW
5. Proportion of births in which LHW was present
6. Proportion of women delivered at institution
7. Proportion of deliveries attended by TBAs
8. Proportion of clean delivery kits used
9. Proportion of women with high-risk pregnancy received referral
10. Proportion of women stabilized or managed before shifting to referral facilities.
11. Proportion of women received comprehensive EmOC services among those who were referred
12. Proportion of newborns seen by CMWs/LHW around day 1, 3, 7 and 28
13. Proportion of newborns resuscitated by CMWs, LHWs and TBAs respectively
14. Proportion of CMWs/LBW able to manage hypothermia
15. Proportion of neonates breastfed in an hour of birth
16. Proportion of neonates avoided pre lacteal feeds
17. Proportion of neonates delayed bathing for at least 6 hours
18. Proportion of neonates who received emollient application
19. Proportion of community participated in support group

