***Demand side interventions***

**a) *Community Mobilization/Community Supports Groups:***

To create awareness in the community and at the household level in intervention clusters, information for empowerment and change (IEC) strategy for women and their husbands through female and male supports groups will be formed/ strengthened. The LHWs will identify and train community facilitators. Female activist will form female support groups and male activists will form male support groups in the LHW catchment area. These activists will enter and raise awareness about MNH and will work with community to identify and invite those most likely to be affected such as poor and marginalized.

These facilitators will be trained on disseminating awareness on antenatal care, identification of danger signs related to pregnancy and recognition for high-risk pregnancies and births (these include maternal malnutrition, illness, short stature, previous perinatal deaths etc.), birth preparedness (skilled birth attendant, facility), essential & immediate newborn care and recognition of danger signs and management low birth weight and sepsis with early and appropriate referral. An emergency fund will be established in community support groups for active referral and transportation of the complicated cases for the provision of EmONC. These community groups will aid in establishing funds from the local resources and families will be asked to contribute whatever is in their capacity, and utilization of these funds will be monitored by the person from community in charge for this activity so that each family benefit equally.

The LHWs and the family members in the intervention community will also be sent informational/educational messages on their mobile phones to highlight the importance of maternal and newborn health. The contact numbers will be collected during the base line survey.

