### Supply side interventions

#### b) Enhanced training of LHWs/ CMWs and TBAs:

The LHWs, CMWs (where present) and TBAs will receive training for early recognition of high risk pregnancies, and identification of need for referral. They will also facilitate transfer to an EmONC facility by identifying and arranging methods of transportation. They would be responsible to stabilize and manage woman/newborn prior to transfer; and communicate with hospital staff for timely and effective management.

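### Process indicators 10 and 11 are taken among referred or transferred women, a group the package itself changes, so they cannot carry the planned between-arm comparison

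*Protocol*

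**What the plan says.** The protocol's section on study outcomes and process indicators lists 19 key process indicators. Indicator 11 is the "Proportion of women received comprehensive EmOC services among those who were referred", so its denominator is stated outright. Indicator 10 is the "Proportion of women stabilized or managed before shifting to referral facilities"; its denominator is not stated, but the wording implies women who are transferred.

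The randomised package acts directly on who is referred:

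- Under enhanced training, community providers "will receive training for early recognition of high risk pregnancies, and identification of need for referral". The package table and the training sections place this in the intervention clusters.
- Of the same providers it says: "They would be responsible to stabilize and manage woman/newborn prior to transfer".
- Under community mobilisation, also for intervention clusters: "An emergency fund will be established in community support groups for active referral and transportation of the complicated cases for the provision of EmONC".

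Strengthening of health facilities, by contrast, goes to both arms (package table; part d of the supply-side interventions).

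The section on research communication and dissemination (R) says that the one-year interim analysis will look at the relative difference between arms on key outcomes, and it names process indicators among them. The same plan is repeated on completion.

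**The concern.** Randomisation makes all pregnant women in the two arms comparable. It does not make referred women comparable when one arm has been trained, funded and equipped to refer more of them. If intervention-arm workers refer at a lower threshold, their referred group contains more women who never needed comprehensive care. If they become better at picking out the women who do need it, the group shifts the other way. Either shift moves indicator 11 without any change in what happens to a woman of given need once she is referred.

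Conditioning on referral also removes the effect of interest. Facilities are strengthened in both arms, so the randomised contrast lies mainly in community mobilisation, recognition and referral. If referrals tripled with unchanged case mix and unchanged care on arrival, indicator 11 would not move at all. The executive summary and the justification ask for evidence on raising uptake of services and cutting delays, but no listed indicator gives comprehensive EmOC per birth or per pregnancy.

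**Working it through.** The protocol gives no figure, target or power for any process indicator, so there is none to reproduce. The check is whether the direction of indicator 11 follows the amount of care delivered.

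**Inputs from the protocol (sample size paragraph).** Cluster size 15,000, birth rate 20 per 1000 per year, three years, ten clusters per arm: 15,000 × 0.020 × 3 × 10 = 9,000 births per arm. This only scales the illustration.

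**Assumed inputs (not in the protocol).** A share n of women need comprehensive EmOC. A share r of women in need is referred: 30% in control, 60% in intervention. A share s = 80% of referred women in need is served, in both arms. A share f of women not in need is referred: 1% in control, varied in intervention. Women not in need do not receive comprehensive EmOC.

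**Formulas.**

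- Indicator 11 = n·r·s / [n·r + (1 − n)·f] = s / [1 + ((1 − n)/n)·(f/r)]
- Comprehensive EmOC per birth = n·r·s

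With n and s fixed, indicator 11 depends only on the ratio f/r. It falls when referral of women not in need rises proportionally more than referral of women in need, ties when both rise equally, and rises otherwise.

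**Results at n = 10%** (900 in need, 8,100 not in need per arm).

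| Arm | f | Referred | Served | Indicator 11 | Per birth |
|---|---|---|---|---|---|
| Control | 1% | 270 + 81 = 351 | 216 | 61.5% | 2.4% |
| Intervention | 8% | 540 + 648 = 1,188 | 432 | 36.4% | 4.8% |
| Intervention | 2% | 540 + 162 = 702 | 432 | 61.5% | 4.8% |
| Intervention | 1.5% | 540 + 121.5 = 661.5 | 432 | 65.3% | 4.8% |

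**Range over need of 5% to 15%.** Control is 49.0% to 67.3%. The intervention arm is 22.6% to 45.6% with f = 8%, equal to control with f = 2%, and 54.2% to 70.1% with f = 1.5%. If f is 5% in both arms, the intervention arm looks better (45.7% against 32.0% at 10% need). Care per birth doubles in every case.

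**Indicator 10, two assumed cases** with 3% (270) of births referred in control and 10% (900) in intervention:

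- Stabilised 50% against 35%: 135/270 against 315/900. The indicator falls, while stabilised women per birth rise from 1.5% to 3.5%.
- Stabilised 30% against 60%: 81/270 against 540/900. The indicator rises, as does the rate per birth, from 0.9% to 6.0%.

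The second case is as plausible as the first, because stabilisation is itself part of the package.

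**The case against.** The strongest reply is that indicator 11 asks a legitimate question: does a referral end in comprehensive care? That stands, and it is why the conditional version should be kept as a description of the referral chain. It does not make the version suitable for comparing arms.

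It can also be said that these are process indicators with no stated test, power or decision rule, and that others (1, 4 to 7 and 12) already measure uptake on women, births, deliveries or newborns. Both statements are correct and limit the weight of the point. A reader should not infer that indicators 10 and 11 are the trial's only evidence on uptake.

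A reader might extend the point to two neighbouring indicators. The documents do not support that:

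- Indicator 9, "Proportion of women with high-risk pregnancy received referral", does not say that the denominator is women recognised by providers. Referral is its numerator, so more referral raises it.
- Indicator 8, "Proportion of clean delivery kits used", is shorthand. Even read literally as a share of kits, it is driven by kit supply and place of delivery rather than by referral.

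The exact denominators of both can be settled in an analysis plan, which is not at hand.

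A last objection is that rates per delivery can reward over-referral. That would hold for a count of referrals, and partly for women stabilised before transfer. It does not hold for women who received comprehensive EmOC, which counts care delivered.

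**Conclusion.** The point holds for indicator 11, whose denominator the protocol fixes as referred women, and by implication for indicator 10. Both condition on an event after randomisation that the package is designed to change, and a between-arm comparison is planned. The comparison is therefore not protected by randomisation, and it leaves out the gain in referral itself.

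A reader might infer that successful referral will make the intervention arm look worse. The documents do not establish that: under the assumptions above, indicator 11 can fall by 25 points (61.5% to 36.4%), tie, or rise by 4 points (61.5% to 65.3%), all with the same doubling of care per birth. The defect is that its sign depends on referral thresholds the trial does not measure. The sizes rest entirely on assumed need, referral and service shares; the dependence on f/r follows from the definition. Primary and secondary outcomes are unaffected.

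**What to change.** For the between-arm comparison, report per all deliveries (or pregnancies) in each cluster (a) women who received comprehensive EmOC and (b) women stabilised or managed before transfer. Take the denominator from the independent surveillance, which counts pregnancies and births in all arms. Take the numerators from the referral tracking and facility records described under routine record keeping, gathered in the same way in both arms. Keep indicators 10 and 11 as worded, labelled as descriptive measures of the referral chain within each arm.

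The cost is mainly wording. The active surveillance list names referrals but not stabilisation or receipt of comprehensive EmOC, so these numerators have to come from the routine records; they must be gathered anyway for the indicators as written. The downside is that the proportions are smaller and do not show quality of care among referred women, which the retained versions cover.

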|                                  | Post Natal Visit                                       | 

▪ Provision of thermal care for low birth weight /pre term babies to prevent hypothermia

▪ Monitoring progress of post pregnancy maternal well being

▪

                                                                                                                                                                                                                                                                                                                                                                                                     | 

• Reinforcement of standard responsibilities

▪ Emollient care (sunflower seed oil)

▪ Early detection and management of common postnatal problems including First dose administration and facilitated referral

▪ Family planning

                                                                   | 

▪ Conduct 4 Post natal visits (1st 1-2 days, 2nd 5-7 days, 3rd 10-14 days, 4th 40th day)

▪ Perform maternal and neonatal examination

▪ Education and counseling

▪ Provision of antibiotic

▪ Provision of weighing scale

 |                                                                                                                                                                                                                                          |

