#### **Delivery of EmONC Package:**

After the training of community and health care providers, the community EmONC package (**discussed in section I**) will be delivered in the intervention clusters primarily through the LHWs and CMWs.

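### The postnatal-contact process indicator counts newborns seen around days 3 and 28, but the package schedules no visit at those ages, so it understates delivery by workers who keep to the schedule.

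*Protocol*

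**What the plan says.** Three places in the protocol bear on postnatal contact.

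- **Study Outcome & Process Indicators, item 12:** "Proportion of newborns seen by CMWs/LHW around day 1, 3, 7 and 28". It is one of 19 items introduced by "The key process indicators include". It is neither a primary nor a secondary outcome. The section heading has these measures assessed at the end of each of three years.
- **Proposed EmONC Package, Post Natal Visit row (intervention arm):** "Conduct 4 Post natal visits (1 st 1-2 days, 2 nd 5-7 days, 3 rd 10-14 days, 4 th 40 th day". The next action in the same cell is "Perform maternal and neonatal examination", so the visits cover the newborn as well as the mother.
- **Routine Record keeping:** two indicators are introduced for programme monitoring, "LHW attendance at birth and an additional post natal visit within 48 hours". The text does not say whether this visit is the first of the four scheduled visits or a fifth.

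Under Delivery of EmONC Package, the package "will be delivered in the intervention clusters primarily through the LHWs and CMWs". The workers who make the scheduled visits are thus the workers whose contacts item 12 counts.

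The protocol does not define 'around'. It also does not say whether item 12 is four separate proportions or a single proportion of newborns seen on all four occasions.

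**The concern.** A process indicator of this kind should show whether the package reached the families. If mortality does not fall, the reader will want to know whether the visits were not made or were made without effect. That requires the indicator to be measured at the times when workers are told to visit.

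Here the two day lists differ. A worker who keeps exactly to the package schedule has no planned contact near day 28 and, depending on what 'around' means, perhaps none that counts for day 3. Contacts at days 10-14 and 40 earn no credit on item 12. A low result could then be read as poor implementation when the schedule had been followed.

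The result would also be seen early. Section R (Research communication and dissemination) puts process indicators into the analysis at the end of the first intervention year, which goes to the funder and other stakeholders.

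**Working it through.** The plan gives no figure for this point, so the check compares the two day lists.

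**Inputs**

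- Visit windows from the package table: days 1-2, 5-7, 10-14 and 40.
- Indicator days from item 12: 1, 3, 7 and 28.
- Tolerance *t* for 'around': not stated, so varied from 0 to 14 days as an assumption.
- Both lists are assumed to count days from birth in the same way.

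**Method.** Each visit falls on a whole day in its window, so the number of on-schedule patterns is 2 × 3 × 5 × 1 = 30. An indicator day *d* is met in a pattern if some visit day *v* satisfies |*v* − *d*| ≤ *t*. In the table below, one visit may count for more than one indicator day.

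| *t* (days) | Day 1 met | Day 3 met | Day 7 met | Day 28 met |
|---|---|---|---|---|
| 0 | 15/30 | 0/30 | 10/30 | 0/30 |
| 1 | 30/30 | 15/30 | 20/30 | 0/30 |
| 2 | 30/30 | 30/30 | 30/30 | 0/30 |
| 3, 5, 7 or 11 | 30/30 | 30/30 | 30/30 | 0/30 |
| 12 or 14 | 30/30 | 30/30 | 30/30 | 30/30 |

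**Day 28.** The distances to the nearest visits are 28 − 14 = 14 days and 40 − 28 = 12 days. No on-schedule visit counts until *t* reaches 12. If the two lists differed by one day in how they count from birth, the smaller gap would be 11 to 13 days, which changes nothing in practice.

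**Day 3.** It lies between the windows ending on day 2 and starting on day 5. At *t* = 1 it is met only when the first visit falls on day 2, which is 15 of 30 patterns. At *t* = 2 it is always met, but only by counting a visit that also serves day 1 or day 7.

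**One visit per indicator day.** If a visit may be used only once, perfect delivery meets 0 to 2 of the four days at *t* = 0, 1 to 2 at *t* = 1, exactly 2 at *t* = 2, and 2 to 3 at *t* = 3.

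**All four days required.** Day 28 fails in every pattern for *t* < 12, so on-schedule visits alone give 0/30 = 0%.

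**The 48-hour visit.** Whether it is the first scheduled visit or an extra one, it falls by day 2. It adds nothing near day 28. For day 3 it counts only if the tolerance reaches back to day 2 or earlier.

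**The case against.** The strongest reply is that this is a loosely worded monitoring item and much of it still works. Days 1 and 7 sit inside scheduled windows. With a tolerance of two days, day 3 is met as well if a visit may count twice. Ending a newborn measure at day 28 is also natural in a trial of neonatal mortality, so leaving the day 40 visit out of item 12 is not in itself an error. All of that stands. It leaves day 28 unexplained, because no ordinary meaning of 'around' spans 12 days. An analysis plan could define the tolerance, but it could not create a scheduled contact between days 14 and 40.

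Four stronger readings may tempt a reader, and the protocol does not support them.

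- *The indicator shows failure under perfect delivery.* That follows for the whole indicator only if all four days are required, which item 12 does not say. Read as four proportions, it fails for certain only at day 28.
- *Perfect delivery can meet only two of the four days.* That needs both a tolerance near two days and a rule of one visit per indicator day. The protocol states neither.
- *Item 12 is the only measure of postnatal coverage, and two scheduled visits go unmeasured.* Routine Record keeping adds the 48-hour indicator and has the workers keep records of their visits, collected monthly by project staff. The day 10-14 and day 40 visits lack a named key indicator, but they may well be recorded. The key list is also introduced as one that includes its items, so it need not be complete.
- *The trial's main result is affected.* Item 12 plays no part in the mortality outcomes, the sample size or the primary analysis.

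**Conclusion.** The mismatch is real and minor. Day 28 in item 12 corresponds to no scheduled visit at any tolerance below 12 days, so workers who follow the package exactly would show near-zero day-28 coverage. It is near zero rather than exactly zero because unscheduled contacts could still occur. Day 3 corresponds to no scheduled window and is met or missed according to a tolerance that the protocol does not state. If all four days are required, on-schedule visits give 0%. The yearly and interim process results would therefore understate delivery in the arm that receives the package.

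This rests on reading the package table as the schedule that workers are to follow, and on both lists counting days from birth. The size of the day 3 shortfall depends on the undefined tolerance; the day 28 result does not, within any reasonable range. The consequence is confined to a process indicator.

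**What to change.** 1. Reconcile the visit days in the package table with those in item 12. State whether the 48-hour visit under Routine Record keeping is the first scheduled visit or a further one. The clinical team should decide the schedule; this review takes no position on which list is right.
2. Define item 12 as a separate proportion for each visit window of the agreed schedule. Replace 'around' with stated first and last days for each window. If the windows do not overlap, one visit cannot be counted twice.
3. Apply the same definition and windows in intervention and control clusters.

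The cost is one indicator definition and the matching field on the data form, provided that it is done before data collection begins. Sample size, outcomes and primary analysis are untouched.
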